## 2. PROJECT SUMMARY

COVID - 19 is a new type of viral pneumonia described in December 2019 in Wuhan - China; it represents a major public health problem due to its rapid spread and the ability to generate severe pneumonia in susceptible patients; at the moment, no specific treatment for the virus has been described, its management being mainly a supportive one. Our objective is to estimate whether treatment with hydroxychloroquine 400 mg / day for 10 days compared to placebo reduces in-hospital mortality in subjects with severe respiratory disease due to COVID-19. Secondary outcomes will be days of mechanical ventilation, requirement of mechanical ventilatory support, days of hospitalization and the cumulative incidence of serious adverse events.

**Design:** Double-blind randomized controlled trial to evaluate the safety and efficacy of hydroxychloroquine for the treatment of severe disease by COVID-19.

**Subjects eligible** Adults older than 18 years with a diagnosis of severe disease (requiring hospitalization or intensive care) of COVID-19 (confirmed by RT-PCR). Subjects will be stratified into two groups (subjects not requiring or requiring ventilatory support at the time of randomization). The analysis will be carried out in R-Rstudio statistical software, considering an interim analysis when half of the sample size is recruited (150 per group).

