**6. Specific protocol interventions:**

- a. Subjects entering the experimental group will receive hydroxychloroquine orally or by nasogastric tube (refer to the protocol procedures manual for the method of crushing tablets and administration via nasogastric tube), 200 mg every 12 hours, for 10 days. The placebo group will receive an identical placebo for 10 days. 10 days are tentatively proposed although the working groups suggest a use between 5 to 14 days; the box of hydroxychloroquine contains 20 tablets of 200mg; We justify the 10-day period because it is somewhere in between the various recommendations and because it is more practical to use one box per subject
- b. Patients in both strata will be treated according to protocols of participating institution under the responsibility of the physician in charge: all interventions, medications for all purposes, or non-drug interventions will be registered.
- c. Patients will be followed up to 30 days after randomization by telephone if discharge occur earlier than Day 30
- d. The Investigator is responsible for detecting, documenting, and recording events that meet the definition of an AE or SAE and remain responsible for following up AEs that are serious, considered related to the study

intervention or study procedures, or that caused the participant to discontinue the study

- e. Adverse events will be reported to CE and to manufacturer of the drug (Sanofi México, S.A. de C.V.)

**Statistical analysis:** The analysis will be carried out in R-Rstudio statistical software. Descriptive statistics will be used according to the type of variable and distribution.

The main outcomes will be compared using parametric and non-parametric tests according to the type of variable and distribution.

Death rate (at 30 days), the primary outcome, will be compared between treatment groups using a logistic regression model, adjusting for age, time from onset of symptoms to randomization, comorbidities (diabetes, hypertension, obesity, tobacco smoking) taking into account the randomization strata.

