From the secondary endpoints, proportion of patients needing mechanical ventilation, will be compared also by a similar logistic regression model as that proposed for 30 days-death rate. Days of mechanical ventilation, days of hospitalization and days of oxygen therapy will be compared in a multivariate model, including an indicator of randomization strata, adjusting for confounding variables (age, time from onset of symptoms to start of treatment, and comorbidities, especially diabetes, obesity, tobacco smoking, hypertension)

We also will compare time to death and time to a negative viral test, adjusting for confounding variables (age, time from onset of symptoms to start of treatment, comorbidities) using the Cox proportional hazards model.

There will be a CMDS, a multidisciplinary advisory group, made up of an expert in statistics, a clinical researcher, an expert in ethics and a clinician related to influenza and coronavirus, none involved in the clinical trial and therefore independent, who in the middle of the Trials will have access to the data and the randomization code to evaluate the data including safety and efficacy results. The study results will remain blinded to trial team and sponsor representatives, so that not to impact final interpretation of the study results.

**Clinical Researcher:** [name], clinical pharmacologist, anesthesiologist and intensivist who will act as coordinator. Dra. [name], Ear nose and Throat specialist and with a masters degree in medical sciences.

**Statistics:** [name], Head of the Department of Epidemiology of INER.

**Ethics:** [name], medical director of INER

**Clinician:** [name], Infectologist, expert in influenza-like infections and now in COVID-19 infection

The aim of the committee is to assess the advantages and disadvantages of continuing the trial in the analysis in the middle of the sample, especially if it is considered ethical to continue the recruitment, given the results found in the middle of the study.

In principle, there are no controlled studies with which to compare but they may appear in the course of the trial.

An interim analysis is planned, upon completing half of the sample, that can identify if a noticeable difference is found in the main outcome measure, demonstrating an advantage in effectiveness, which, due to its magnitude, leads to stopping the trial.

Also, to indicate significant adverse effects or toxicity.

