The final statistical analysis will be carried out taking into account this intermediate analysis. The CMDS will provide a written report (not accessible to anyone outside the CMDS) of its observations. It will be considered sufficient to stop the trial because efficacy in the first interim analysis (1 interim and final), if  $P < 0.0054$  and the final analysis will remain significant with  $p < 0.0492$  (according to O'Brien-Flemming). It can also be stopped if probability of success at the final analysis, given the interim results, is too low.

1. **Sample size:** Mortality reported in severe COVID-19 ranges depending on the source, but in China among hospitalized patients with pneumonia has been reported from 4-15% (1,2,4). The WHO suggests at least 400 subjects for sample estimation in clinical trials evaluating therapies for COVID-19, although severe outcomes or deaths increase considerably in hospitalized patients or those in intensive care as those eligible for this trial. (3). At the moment, many behavioral characteristics and outcomes of COVID-19 are unknown, especially in our setting; For this reason, we used the estimate of a mortality of around 15% in severe COVID-19 with a 50% reduction in mortality with treatment, obtaining in the sample calculation a number of subjects similar to that recommended by the WHO.

- a. 2-tailed significance level 95, alpha 5%
- b. Potency (1-beta, chance of detection): 80%
- c. Treaties vs. controls 1: 1
- d. Estimated mortality in controls 15%
- e. Estimated mortality in experimental 7.5%, reduction in mortality of 7.5%, which is 50% (RR 0.5).

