## **3. Exclusion criteria:**

- a. Positive pregnancy test.
- b. Contraindication to start or continue hydroxychloroquine (including but not limited to history of pre-existing maculopathy, history of prolonged QTc syndrome or other cardiac condition that, by the judgement of the Investigator, would put the patient at higher risk for QTc prolongation or sudden cardiac death, severe skin reactions, patient with uncorrected hypokalemia or hypomagnesemia, a contraindicated drug interaction according to local drug labelling, , known hypersensitivity to hydroxychloroquine or chloroquine, severe hepato-cellular disorder, severe renal insufficiency
- c. Previous COVID-19 infection
- d. Decision of the responsible doctor not to participate.
- e. Transfer of the patient to another hospital unit
- f. Current or last month treatment with hydroxychloroquine.

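### The protocol provides for only one comparison of safety by arm, at half the sample, and does not name the CMDS as a recipient of adverse events; earlier safety-only reviews would be a cheap improvement

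*Protocol*

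**What the plan says.** All references are to the Protocol.

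- **One look.** Section 2 describes "considering an interim analysis when half of the sample size is recruited (150 per group"). The stopping paragraph in section 3.4 (Statistical analysis) confirms the count: "because efficacy in the first interim analysis (1 interim and final").
- **Who sees data by arm, and when.** The Statistical analysis text says that the CMDS "in the middle of the Trials will have access to the data and the randomization code", to evaluate safety and efficacy. Its purpose is stated as: "The aim of the committee is to assess the advantages and disadvantages of continuing the trial in the analysis in the middle of the sample". The same text adds that the interim analysis should also indicate significant adverse effects or toxicity.
- **Routing of adverse events.** Section 3.4, item 6e: "Adverse events will be reported to CE and to manufacturer of the drug". The CMDS is not mentioned there. Item 6d makes the investigator responsible for detecting, recording and following up events.
- **Blinding.** The treating team and outcome evaluators are blinded to group (section 3.4, item 1). The trial team and sponsor representatives are blinded to results (Statistical analysis).
- **Recognised risk.** Exclusion criterion 3b refers to cardiac conditions that "would put the patient at higher risk for QTc prolongation or sudden cardiac death". Section 3.3.1 lists safety as a specific objective.

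**The concern.** Mortality is expected to be substantial in both arms (15% is assumed for controls). Single case reports therefore cannot show whether deaths are more frequent on the drug; only a comparison by arm can. The same holds for serious adverse events in very ill patients. The protocol gives the means for that comparison to one committee, at one time, and does not place that committee on the reporting route for adverse events.

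Followed as written, the first half of the trial runs without anyone being assigned to look for an imbalance. This is so even though the protocol itself names QTc prolongation and sudden cardiac death as risks. What is at stake is how long a real excess, particularly a large one, could continue before the committee had a planned chance to see it.

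**Working it through.** **Inputs.** From the Protocol: 600 patients, 300 per group (sample size section); interim at 150 per group (section 2); 8 months of execution (section 7); primary outcome at 30 days (section 3.4, item 3); control mortality 15%, experimental 7.5%, two-sided 5%, 80% power (sample size section). Assumptions: even accrual, and mortality on drug of 20%, 22.5%, 25% or 30% in the harm illustrations.

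**Step 1: the plan's own figure.** The Kelsey formula, (1.960 + 0.842)² × 2 × 0.1125 × 0.8875 / 0.075², gives 278.6 per group (stated 280). Fleiss gives 278 (stated 279), and with continuity correction 304 (stated 305). The stated figures reproduce closely. Rounding to 300 per group gives 600, so the look at half the sample is at 300 patients.

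**Step 2: when the look falls.**
- Accrual: 600 / 8 = 75 patients a month.
- 300 recruited: 300 / 75 = month 4.
- 300 with 30-day outcome: month 4 + 1 = month 5, when 75 × 5 = 375 patients are enrolled.

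If enrolment has to finish in 7 months to leave room for follow-up, the times become 3.5 and 4.5 months. The first review by arm is therefore about 4 to 5 months in.

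**Step 3: what could accumulate first (illustration).** Expected excess deaths among the first 150 treated = 150 × (assumed rate − 0.15).

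| Assumed mortality on drug | Excess deaths |
|---|---|
| 20% | 150 × 0.05 = 7.5 |
| 22.5% | 150 × 0.075 = 11.25 |
| 25% | 150 × 0.10 = 15 |

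**Step 4: what earlier reviews could detect.** The calculation is the chance of one-sided p < 0.05 in the harm direction. It uses the pooled two-proportion z test, exact enumeration of both binomial counts, control mortality 15%, and all outcomes known.

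| Patients randomized | 22.5% v 15% | 30% v 15% |
|---|---|---|
| 60 (30 per arm) | 19% | 42% |
| 150 (75 per arm) | 32% | 72% |

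On this accrual, those reviews would come at 60/75 = 0.8 and 150/75 = 2 months of recruitment, against 4 months for the planned look. They would catch moderate harm in a minority of cases and large harm considerably more often.

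**The case against.** **Individual events are not hidden.** Investigators must detect and record events (item 6d), ECG or cardiac monitoring is among the routine tests (item 5c), and exclusion criterion 3b covers contraindications to starting or continuing the drug. This stands. What is missing is the comparison between arms, not sight of the events themselves.

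**The committee is not held to an efficacy p-value when judging harm.** A reader might infer that P < 0.0054 is also the bar for harm, because it is the only numeric interim threshold. The text does not support that: the rule begins "It will be considered sufficient to stop the trial because efficacy in the first interim analysis (1 interim and final), if", and harm is left to the committee's judgement, including whether continued recruitment is ethical. Power figures that apply 0.0054 to harm would test a rule that the plan does not contain.

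**The low-probability-of-success stop would often apply.** With 22.5% against 15% at 150 per arm, and an assumed conditional-power cut-off of 20% (the protocol gives none), the criterion is met in about 95% of trials under the design effect and over 99% under the current trend. At 20% against 15% the figures are about 86% and 98%. So the planned look is not toothless, but this protection acts only at that same look.

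**The early reviews have low power**, as step 4 shows, and how often to look is partly a matter of preference. This also stands and limits what can be claimed for the fix.

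**A charter or text not seen might add reviews.** Text between sections 3 and 5 was not available for this review. The visible protocol cites no charter, however, and it fixes both the number of looks and the committee's aim.

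**Conclusion.** The point holds in a limited form. The visible text provides for one review by arm, at 150 per group, and leaves the CMDS out of adverse event reporting. No comparison of deaths, serious adverse events or cardiac events by arm is planned before about 300 patients, at roughly 4 to 5 months. The timing rests on even accrual. The 7.5 to 15 excess deaths rest on assumed drug-arm mortality of 20–25%; they are not a forecast, nor a count of deaths that the fix would avert.

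Two further readings go beyond the documents:

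- **That adverse events go to blinded recipients.** The protocol grants the code only to the CMDS, but it does not state the blinding status of the CE or the manufacturer.
- **That the committee's conclusion cannot reach anyone who can act.** The protocol says "The CMDS will provide a written report (not accessible to anyone outside the CMDS) of its observations". It also calls the CMDS an advisory group on whether to continue, and a confidential report does not bar it from giving a recommendation.

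This is a worthwhile and inexpensive improvement in participant protection. It is not an error that threatens the efficacy conclusion.

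**What to change.** 1. In the Statistical analysis text of section 3.4, add safety-only CMDS reviews by arm (deaths, serious adverse events, cardiac events) before the midpoint, for example at about 60 and 150 randomized. State that no efficacy test is done at these reviews, so the efficacy alpha is not affected.
2. In section 3.4, item 6e, add the CMDS as a recipient of serious adverse events, with access to the randomization code from the start rather than only at mid-trial.

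A numeric harm guideline, or a split between closed and open committee reports, is optional and can be left to a charter.

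The cost is amendment wording, two short extra meetings of the existing committee, and simple tables by arm. The amendment should say plainly that these reviews have limited power for moderate harm, so that an unremarkable early review is not taken as evidence of safety.

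### The stated interim and final thresholds (0.0054 / 0.0492) have the O'Brien-Fleming shape but spend about 0.0513 two-sided, slightly more than the planned 0.05

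*Protocol*

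**What the plan says.** All the inputs needed to check the stopping boundary are in the protocol.

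- **Overall level.** The sample size item in section 3.4 gives "2-tailed significance level 95, alpha 5"%.
- **Looks.** The statistical analysis text in section 3.4 has "1 interim and final", that is, two analyses.
- **Timing.** The same text states "An interim analysis is planned, upon completing half of the sample". Section 2 (Project Summary) agrees: "considering an interim analysis when half of the sample size is recruited (150 per group"), with 300 per group planned in total.
- **Thresholds.** Stopping for efficacy and final significance are set at "P < 0.0054$ and the final analysis will remain significant with $p < 0.0492", "according to O'Brien-Flemming".
- **Futility.** "It can also be stopped if probability of success at the final analysis, given the interim results, is too low". No cut-off is given, and the provision is worded as an option.

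**The concern.** A group-sequential boundary is meant to keep the chance of a false positive, over all looks together, at the planned level. For one interim at half the sample and a two-sided 5% level, the exact O'Brien-Fleming pair is about 0.0052 and 0.0480. The protocol's levels are both a little more generous than these, so together they must spend more than 5%.

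These two numbers decide whether the trial stops early and whether a mortality benefit is declared. A final p-value between 0.0480 and 0.0492 would be called significant under a rule that does not hold its stated 5%. Anyone can recompute this from the protocol, and a correction made after unblinding would carry little credibility.

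**Working it through.** **Inputs (protocol sections 2 and 3.4).** Overall two-sided α = 0.05; two looks; interim at information fraction t = 0.5 (150 of 300 per group); interim p < 0.0054; final p < 0.0492; mortality 15% against 7.5%.

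**Step 1: shape of the stated pair.** With z = Φ⁻¹(1 − p/2):
- interim: Φ⁻¹(1 − 0.0027) = 2.782
- final: Φ⁻¹(1 − 0.0246) = 1.967
- ratio: 1.4145

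O'Brien-Fleming with two equal looks uses c₁ = √2·C and c₂ = C, a ratio of 1.4142. The pair therefore comes from one boundary of this family, with C = 1.967.

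**Step 2: overall error of the stated pair.** Under the null, Z₁ and Z₂ are bivariate normal with correlation √0.5. Then

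α = 1 − ∫ from −c₁ to c₁ of φ(x)·[Φ((c₂ − √0.5·x)/√0.5) − Φ((−c₂ − √0.5·x)/√0.5)] dx.

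With c₁ = 2.782 and c₂ = 1.967, α = 0.0513: 0.0054 at the interim plus 0.0459 at the final. Rounding of the printed thresholds moves this only between 0.0512 and 0.0514, and a simulation of 40 million draws also gives 0.0513. The planned 0.05 is not reproduced.

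**Step 3: the constant that does give 5%.** Solving α(√2·C, C) = 0.05 gives C = 1.977, so c₁ = 2.797 (p = 0.0052) and c₂ = 1.977 (p = 0.0480). Changing one threshold alone:
- keep 0.0054 at the interim: the final level must be 0.0479
- keep 0.0492 at the final: the interim level must be about 0.0026

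**Step 4: other readings of the rule.**

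| Reading | Error |
|---|---|
| Symmetric two-sided stopping at t = 0.5 | 0.0513 |
| Interim stops for benefit only, final two-sided | 0.0502 (benefit side 0.0256, harm side 0.0492/2 = 0.0246) |
| Both thresholds read as one-sided p-values | 0.0509, one-sided |
| Interim at t = 0.7 instead of 0.5 | 0.0500 |
| Binding futility at z < 0 | benefit side 0.0253 |
| Binding futility at z < 0.5 | benefit side 0.0242 |

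Only a later interim or a sufficiently strict binding futility rule brings the error within the plan. The first contradicts the stated timing, and the second is not in the protocol.

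**Step 5: power cost of correcting.** The drift at 300 per group is 0.075 / √[(0.15·0.85 + 0.075·0.925)/300] = 0.075/0.02562 = 2.928. Two-look power is 83.3% with 0.0054 / 0.0492 and 83.1% with 0.0052 / 0.0480 (0.8333 against 0.8307, about 0.3 points).

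**The case against.** The strongest reply is that the effect is too small to matter, and much of it stands.

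- **One-directional stopping.** The interim is described as a look for benefit. If it cannot reject for harm, the two-sided error is 0.0502, an excess of about 0.02 percentage points. This is a fair reading and belongs in the statement of size. It does not remove the excess: the benefit side is still 0.0256 against 0.025.
- **Approximation error.** Exact binomial enumeration with a treatment-only logistic Wald test and symmetric stopping gives 0.0493 for the stated pair at 15% mortality in both arms, and 0.0489 at 11.25%. At 25–30% mortality it gives 0.0506–0.0508, and an unadjusted chi-square test at 15% gives 0.0516. So the actual error depends on the test and the event rate, and a tenth of a point is within that variation. The enumeration omits the planned covariates and is only indicative. A boundary is set on the nominal scale, however, and there the pair is miscalibrated.
- **Practical reach.** Under the design alternative, the chance of continuing past the interim and then landing between 0.0480 and 0.0492 is about 0.26%.
- **Futility.** An optional stop for low probability of success can only lower the error. With no cut-off and no binding status, it cannot be credited with a definite amount.

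**Conclusion.** The point holds as a minor calibration error. The nominal overall two-sided type I error is 0.0513 with symmetric stopping and 0.0502 with stopping for benefit only, against a planned 0.05. This rests on the normal approximation, an interim at half the information and no binding futility rule. It matters only for a result near the boundary.

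Two stronger readings are not supported.

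- A reader might infer that the two thresholds come from different rules and do not belong together. The ratio 1.4145 rules this out: the shape is right and only the constant is off.
- A reader might infer from "The main outcomes will be compared using parametric and non-parametric tests according to the type of variable and distribution" that the test behind the thresholds is left open, so that a choice between tests could inflate the error further. The protocol goes straight on to assign an adjusted logistic regression model to 30-day death, naming it as the primary outcome. The general sentence covers outcomes by type of variable and does not permit a choice of test for mortality.

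**What to change.** Before the interim look, make one of two changes in the stopping rule of section 3.4:

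- replace the pair with interim p < 0.0052 and final p < 0.0480 (exact O'Brien-Fleming, two equal looks); or
- name a Lan-DeMets O'Brien-Fleming-type spending function and compute the final level from the information fraction actually reached. Applied at 0.025 per side, it gives 0.0031 / 0.0490 at half information. The per-side level should be written down, because the same function applied to a two-sided 0.05 gives 0.0056 / 0.0478.

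It would also help to say whether the interim can reject in one direction or both, and that the futility provision is non-binding if that is the intention.

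The cost is two numbers and a sentence. With the first option, power at 300 per group goes from 83.3% to 83.1%, still above the stated 80%, and the sample size of 600 stays as it is.
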